### Randomization

Participants will be randomized to the intervention or control group on a 1:1 basis stratified by baseline measure of frailty (ie, frail or not frail according to the FRAIL score) [28,29] and using permuted blocks of sizes 4 and 6. The statistician has generated a randomization list using the RandomiseR package in R software (R Foundation for Statistical Computing) [32]. The randomization list will be input into the REDCap (Research Electronic Data Capture) [33] database, which captures participant demographic and baseline data and survey findings (Multimedia Appendix 1). The statistician and principal investigators will be unaware of patient allocation until after the completion of the study.

### Recruitment

A multipronged approach will be used to identify potential participants. We will use clinician networks (eg, GPs, cardiologists, geriatricians, and allied health professionals) and a variety of direct approaches to the community to recruit a wide spectrum of participants from various demographic backgrounds living in wide geographical areas across Australia. Communications will be sent to practice managers seeking their assistance in disseminating introductory letters, leaflets, flyers, and posters to their clinicians. The practice managers may also disseminate the information to their patients through their usual channels of communication, including displaying them in waiting rooms, websites, newsletters, or in electronic format or hard copy. The decision to contact the research team will be at the discretion of the patients. In addition, a direct community approach will be used. The research poster and leaflets will be disseminated in local community centers such as the Returned and Services League Australia and places of worship. People interested in the study will initiate contact with the study team directly by email or phone to receive further information. We will also list the study with third-party recruiters such as HealthMatch [34] and Join US [35]. Individuals who contact the research team will be screened for eligibility and provided with further explanations about the study. We will inform GPs about their patients who enroll in the study.

### Participant Consent and Enrollment

The research team will confirm the eligibility of interested individuals against the inclusion and exclusion criteria over the phone. Eligible individuals will be provided with participant information statements and consent information and given time to read the information. Research personnel will answer individuals’ questions. Participants will provide verbal consent to a member of the research team who will electronically sign off the consent form and keep the form in the secured university computer drive.

### ECG Central Monitoring System

Qualified and trained study personnel, including a cardiac technician and clinical monitoring personnel with medical qualifications, will remotely review all ECGs and compare their diagnosis with the device’s automated diagnostic algorithm. If the ECGs are normal or have minimal abnormalities and the personnel are certain of their diagnosis, the ECGs will not be referred to a cardiologist. However, the personnel will refer all abnormal ECGs for diagnosis confirmation, or uncertain ECG abnormalities for clarification of diagnosis, to cardiologists or cardiac electrophysiology specialists. Participants’ ECGs will be classified into *low, moderate, high, and severe abnormalities* and managed as shown in Table 1. The research team will notify the participants and their GPs of AF or other clinically significant ECG abnormalities. A copy of an abnormal ECG will be forwarded to their GP. When an AF diagnosis is confirmed by the research team, the participant will be advised to see their GP. The participant will exit the screening program or opt to continue the monitoring program. The research team will contact the GP to obtain information about the treatment given to the patient.

**Table 1 table1:** Electrocardiogram (ECG) classification and management plan.

ECG findings	Classification	The study team will take the following actions
First-degree heart block	Low critical abnormality	If PR interval >300 milliseconds, notify and send ECG to GP^a^ within a week If PR interval is between 201 and 300 milliseconds, notify and send ECG to GP within the duration of participant’s enrollment in the study
Ectopic heartbeats (atrial ectopic and ventricular ectopic)	Low critical abnormality	As these are common and noncritical findings, notify GP at the end of the study
Atrial fibrillation, atrial flutter, nonsustained ventricular tachycardia, bradycardia <40 bpm^b^, second-degree heart block, nonsustained supraventricular tachycardia	Moderate critical abnormality	Notify and send ECG to GP within a week Advise patients to see their GP as soon as possible Contact patient to confirm review with their GP in the subsequent week
Significant ECG abnormalities that need urgent medical attention (eg, suspected ST elevation)	High critical abnormality	Consult cardiologists in the research team to confirm the diagnosis, and where necessary, adjudicate suspect ECGs Notify and send ECG to GP within 3 working days Advise patients to see their GP as soon as possible Contact patient to confirm review with their GP in the subsequent week
Potentially life-threatening arrhythmia or abnormality (eg, third-degree heart block)	Severe abnormality	Consult cardiologists in the research team to confirm diagnosis Advise patients to present to their local emergency department immediately Notify and send ECG to GP on the same day Contact patient to confirm review with their GP in the subsequent week
ECGs without any of the above abnormalities	Normal	Review ECG report (including normal and the above abnormal findings) in monthly team meeting

^a^GP: general practitioner.

^b^bpm: beats per minute.

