### Objective

Our study objectives are to (1) compare AF ascertainment rates in the intervention and control groups; (2) evaluate the feasibility of the intervention, including assessing participant satisfaction, acceptability, barriers, and enablers and how frailty influences these assessments; and (3) assess agreements between the ECG device automatic algorithm and clinician interpretation.

Alongside these objectives, the specific objectives of the process evaluations are as follows:

To assess the fidelity of the screening program (ie, whether the intervention was delivered as intended), participant engagement with the intervention in terms of the frequency of ECG recordings, and reach (eg, the socioeconomic and frailty profiles of participants and how these profiles affect the engagement and outcomes)To evaluate the feasibility of the screening program from the perspective of participants and clinicians to gain a deeper understanding of barriers and enablers; this includes an examination of the mechanisms of impact; that is, an examination of the potential causal mechanisms through which the intervention results in the adoption of self-screening by understanding how patients and clinicians interact with the screening programTo explore any factors external to the screening program that may have affected implementation (ie, the community-dwelling environment, access to health care services, and GP views and attitudes), including identification of resources and implementation processes required for effective uptake and implementation of the screening program

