### Sample Size

In computing the sample size required to assess the primary feasibility outcome, we will evaluate the proportion of participants reporting being satisfied or very satisfied that their heart rhythm was monitored in the past 6 months in the intervention group versus the control group. We arbitrarily set that 50% of the participants in the control group will be satisfied or very satisfied. With reference to the literature that reported a proportion of 67% [30] to 82% [31] of older people were satisfied or very satisfied with the use of technology-enabled monitoring at home, we postulate that there will be an absolute 30% increase in satisfaction in the intervention group compared with the control group. Our study will have 80% power, using a 5% level of significance, to detect an absolute difference of 30% in satisfaction between the 2 groups. A sample size of 100 participants aged ≥75 years is required to assess the primary feasibility outcome

To calculate the sample size required to evaluate the primary clinical outcome of AF detection rate, we set an AF detection rate of 10% in the intervention group and 1% in the control group, in accordance with a recent study [22]. At 80% power, a 2-sided test, and α .05, we estimate that a sample of 200 participants will be needed to detect a significant difference in AF detection between the intervention and control groups. Therefore, a total of 200 participants will be recruited for this trial to assess the primary clinical outcome.

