### Analysis

All analyses will be conducted according to the principle of intention-to-treat. Continuous variables will be presented as mean (SD) or median with IQR and categorical variables as frequency and percentage. The key outcomes, namely participant satisfaction in the AF screening program, usability of the screening program, and the incidence of new AF detected over 6 and 12 months, will be reported as frequency and percentages and will be compared between the intervention and control groups using the chi-square test. Comparisons between groups (intervention and control) for other outcomes will be assessed using the chi-square test or Fisher exact test for categorical variables and Student *t* test or Mann-Whitney test for continuous variables as appropriate. We will consider 2-tailed *P*<.05 as statistically significant. The agreement between the ECG device automatic algorithm and clinician interpretation will be evaluated using κ statistics. Subgroup analyses will be performed based on age, gender, and location. Subgroup analysis by frailty will be performed to examine the potential impact of frailty on the outcomes, feasibility, and acceptability of the program. The actual operational costs of delivering the project will be recorded and verified using invoices and receipts, including the costs of personnel involved in interpreting ECGs, which will be computed based on their hourly wages and the time they spent in their roles in this program. The resultant costs will be compared with the costs reported in the literature on the costs associated with the detection of AF in a similar older population. Missing data will be identified, and its causes will be described. Sensitivity analysis will be performed to examine the robustness of the findings [39].

Qualitative evaluation will be reported according to the COREQ (Consolidated Criteria for Reporting Qualitative Research) guidelines [40]. Interviews with patients and GPs will be thematically analyzed using an inductive approach [41]. Themes will be interpreted through the critical realism lens [37] and compared with the literature [42,43]. We will triangulate the quantitative and qualitative findings [44] from patient participants and GPs to acquire an in-depth understanding of the barriers to and enablers of implementing the screening program.

The process evaluation components [36], explanatory data, and anticipated outcomes are summarized in Table 2.

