**Agreement in electrocardiogram interpretations**
Number of consultations and percentages of agreement between the monitoring personnel and cardiologists in clarifying uncertain electrocardiogram abnormalities—logs of all interactions

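### The ECG review workflow does not ensure that the clinician's reading is fixed before the device result is seen, so the device–clinician kappa may be inflated

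*Protocol article*

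**What the plan says.** The Objective section lists, as item 3, to "assess agreements between the ECG device automatic algorithm and clinician interpretation". The Analysis section names the statistic: "The agreement between the ECG device automatic algorithm and clinician interpretation will be evaluated using κ statistics".

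How the clinician's reading arises is described only under ECG Central Monitoring System. A cardiac technician and medically qualified monitoring personnel "will remotely review all ECGs and compare their diagnosis with" the device's algorithm. Abnormal ECGs go to cardiologists or electrophysiology specialists for confirmation, and uncertain abnormalities go to them for clarification. If an ECG is normal or minimally abnormal and "the personnel are certain of their diagnosis, the ECGs will not be referred to a cardiologist", the first reading is the only clinician reading.

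The only masking stated is under Randomization: "The statistician and principal investigators will be unaware of patient allocation until after the completion of the study". It concerns treatment allocation, not the device output.

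**The concern.** Kappa corrects observed agreement for the agreement expected by chance between two raters who judge independently. Here one rater is the algorithm and the other is a person whose task includes comparing their own diagnosis with the algorithm's. If that person sees the label before settling the diagnosis, a doubtful tracing can be pulled towards the label. Kappa then partly measures the reader's deference to the device.

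The readings are made for triage, where sight of the device result may be useful. They are then used again as one of the two ratings for a named objective, and the two purposes are not separated. Independence is settled when a reading is made, so a later analysis plan cannot supply it for readings made with the label in view. New masked readings would be needed.

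The Introduction asks how much time services need to review large volumes of ECG data and how resources could be used better. Device–clinician agreement bears on that question, and an inflated kappa would make the algorithm look like a closer substitute for the clinician than it is.

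**Working it through.** **What the text settles.**

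| Question | What the article states |
|---|---|
| Who reads? | Study personnel read all ECGs |
| Who compares with the device? | The same personnel |
| Is the diagnosis recorded before the device result is shown? | Not stated |
| Are readers masked to the device result? | Not stated; the only masking concerns allocation |
| Is there a second clinician reading? | Only for abnormal or uncertain ECGs; masking of these readers is not stated |
| Does Textbox 1 supply a masked comparison? | No. Its agreement entry is "percentages of agreement between the monitoring personnel and cardiologists in clarifying uncertain electrocardiogram abnormalities", which is a different pair of raters |

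The last row is a separate matter of which raters are compared. It is noted here only because it does not fill the gap.

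**Volume of readings.** At one ECG per weekday and full adherence, 100 intervention participants over 12 months give 100 × 52 × 5 = 26,000. A further 100 control participants over 6 months give 100 × 26 × 5 = 13,000. The total is about 39,000.

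**Direction and size.** The article gives no expected kappa, precision target or number of ECGs for this objective, so there is no stated figure to reproduce. Every input below is an assumption.

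Kappa = (Po − Pe)/(1 − Pe), where Po is observed agreement and Pe is chance agreement from the margins.

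*Illustration A.* Independent clinician reading taken as the reference; 2% of ECGs read as AF; device sensitivity 90%, specificity 97%.
- Both AF: 0.02 × 0.90 = 0.0180
- Device AF only: 0.98 × 0.03 = 0.0294
- Clinician AF only: 0.02 × 0.10 = 0.0020
- Neither: 0.98 × 0.97 = 0.9506
- Po = 0.9686
- Pe = 0.0474 × 0.02 + 0.9526 × 0.98 = 0.9345
- Kappa = 0.0341/0.0655 = 0.52

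Now let the reader adopt the device label in 10% of the discordant ECGs. The cells become 0.02094, 0.02646, 0.0018 and 0.9508. Po = 0.97174, Pe = 0.93202, and kappa = 0.0397/0.0680 = 0.58.

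| Share of discordant ECGs switched | Kappa, specificity 97% | Kappa, specificity 99% |
|---|---|---|
| 0 | 0.52 | 0.75 |
| 10% | 0.58 | 0.78 |
| 20% | 0.64 | 0.80 |
| 30% | 0.70 | 0.83 |

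*Illustration B.* The reader also errs, and device and reader are independent given the true rhythm. AF share is 1%, 2% or 5%. Sensitivity/specificity pairs are device 0.90/0.95 with reader 0.95/0.99, or device 0.95/0.97 with reader 0.98/0.995. This gives six settings.

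| Share switched | Kappa, range over six settings | 2% AF, device 0.90/0.95, reader 0.95/0.99 |
|---|---|---|
| 0 | 0.21 to 0.70 | 0.34 |
| 10% | 0.32 to 0.74 | 0.43 |
| 25% | 0.47 to 0.78 | 0.55 |
| 50% | 0.68 to 0.86 | 0.72 |

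Kappa rises with the share switched in every setting. The size depends on a switching share that the documents do not give, and it is zero when readings are independent. Both models apply one switching share to all discordant tracings, clear or doubtful, and neither models specialist referral. They show direction only.

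**The case against.** The strongest reply is that the article never says the reader sees the label first. Comparing one's diagnosis with the device's presupposes having a diagnosis, so reading first and comparing afterwards fits the sentence at least as well. The order may also be set out in the full protocol, which the article condenses. This stands. A reader might infer that the ratings are not independent and that kappa will be biased upward, but the documents support neither statement.

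Second, abnormal and uncertain tracings go to specialists, so the doubtful ones get a further look. This is true and limits first-reader drift. It does not remove the problem: the specialists are not stated to be masked, the article does not say which reading enters kappa, and a tracing called normal with certainty, perhaps because the device also said so, never reaches them.

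Third, the illustrations rest wholly on assumed inputs. That also stands, and no size can be claimed from them.

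Fourth, a reader might infer that the harm is irreversible, or that the trial will use kappa to drop a review step. Neither is supported. If the transmitted tracings are retained, they can be re-read masked, and no section makes kappa a decision rule. Agreement is also not a primary outcome.

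What remains is more than missing detail. A triage workflow that includes a comparison with the device does not produce masked readings by default, and the article uses that workflow's output for a numbered objective.

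**Conclusion.** The point holds in conditional form. The described workflow has the same personnel read and compare, and it does not ensure that the clinician's diagnosis is fixed before the device result is seen. It therefore does not ensure the independent ratings that the planned kappa needs. If the label is visible first, kappa may be inflated. The illustrative increases (for example 0.52 to 0.58, or 0.34 to 0.43, at 10% switching) show a plausible direction under assumed inputs and are not estimates for this trial. If the reading is already recorded first, there is no inflation and one sentence saying so would close the point. The AF detection and satisfaction comparisons and the sample size of 200 are not affected. This is an inexpensive improvement to one secondary feasibility outcome.

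**What to change.** For the agreement objective, have the existing reader record a diagnosis before the device result is shown, and state this in the ECG Central Monitoring System section. The comparison with the device then follows as planned.

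A reading-order rule cannot reach readings already made (112 participants had been enrolled by December 2021), and the portal may not be able to hide the label. In either case, have the existing readers re-read a random sample of stored tracings without the device label, and base kappa on these masked readings only. If the sample is stratified by device label so that it contains enough flagged ECGs, weight kappa back to the sampling fractions.

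Routine safety review is unchanged. The cost is some added reading time and, if a sample is used, fewer ECGs in the kappa and so a wider interval.

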Research assistants will take participants through the steps of recording an ECG. Participants will record a single-lead ECG trace by placing 2 fingers of each hand steadily on 2 small touchpads (3 cm × 3 cm) of the device for 30 seconds on weekdays. The ECG device will be connected to the mobile phone wirelessly via the Kardia app that they have downloaded. An ECG trace will appear on the participants’ mobile phones, and participants will be able to record notes in the ECG trace. We will encourage them to note the activities they performed before recording the ECG. The ECG and notes will be automatically transmitted to the central monitoring portal. The training conducted over the telephone or video call between research assistants and participants will take approximately 30 to 60 minutes per participant. In the context of the COVID-19 pandemic, all study-related procedures will be conducted remotely using phone calls or video calls (if participants have access to and prefer this modality). To ensure that participants are confident in using the device, research assistants will call each participant to confirm that they are able to record an ECG. Participants will be encouraged to have a family member who may assist them in the process. After the training, participants will also receive an SMS text message with a weblink to an instructional video created by the device manufacturer. The short training video will serve as a reference for participants to refresh their memory on how to record a single-lead ECG. The research team will contact participants if they have not recorded any ECGs for 3 consecutive days to find out and address the causes, if possible.

Before commencing the study, participants will be advised that in the event of experiencing symptoms (eg, syncope, chest pain, palpitations, and shortness of breath) that are severe in nature or that are of concern to the participants, to present to their local medical physician or hospital for assessment as soon as possible.

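### Table 1 allows up to 3 working days to notify the GP of a High finding that it labels urgent, although the GP is the only clinician that row sends the patient to

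*Protocol article*

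**What the plan says.** Table 1 grades ECG findings and lists the team's actions for each grade.

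- **High row.** It covers "Significant ECG abnormalities that need urgent medical attention (eg, suspected ST elevation"). The actions, in order, are: consult the study cardiologists and adjudicate suspect tracings where necessary; "Notify and send ECG to GP within 3 working days"; "Advise patients to see their GP as soon as possible"; and check in the following week that the GP review took place.
- **Severe row.** The actions, in order, are: "Consult cardiologists in the research team to confirm diagnosis"; send the patient straight to the emergency department; "Notify and send ECG to GP on the same day"; and make the same check in the following week.
- **Moderate row** (which includes AF). The GP limit is "Notify and send ECG to GP within a week", with the same advice to the patient to see the GP promptly.

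Three other places bear on the point. Under Intervention Group, "An ECG trace will appear on the participants’ mobile phones", and participants with symptoms are advised beforehand, if these are ones "that are severe in nature or that are of concern to the participants, to present to their local medical physician or hospital". Under Recruitment, GPs are told which of their patients have enrolled. Under Anticipated Research Outcomes and Impacts on Clinical Practice and Policy, GPs are said to have access to the participating cardiology team.

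**The concern.** The High row depends on the GP visit. The GP is the only clinician to whom the patient is directed, and the row's label says the finding is urgent. The outer limit for telling that GP is nevertheless counted in working days. Staff could follow the table exactly while the GP sees the patient without the team's notice and interpretation, or while the patient is still waiting to be told. In the Severe row another clinician sees the patient first, and there the GP must be told the same day. What is at stake is timely care for a participant with a High finding. No estimate, test or sample size depends on it.

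**Working it through.** No statistical figure is involved. The check compares the rows and converts the limit to calendar days.

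**1. The rows side by side**

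| Row | Ceiling for GP notice | Where the patient is sent | Cardiologist step in the row |
|---|---|---|---|
| Moderate | a week | GP | none listed |
| High | 3 working days | GP | confirm; adjudicate if needed |
| Severe | same day | emergency department | confirm |

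The ceilings shorten as the grade rises, so the order is coherent. The mismatch lies within the High row, between its label and destination on one side and its GP limit on the other.

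**2. The limit in calendar days**

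Assumptions: working days are Monday to Friday, there are no public holidays, and the day of review is day 0. The article states no clock start.

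- Reviewed Monday: ends Thursday, 3 days.
- Reviewed Tuesday: ends Friday, 3 days.
- Reviewed Wednesday: ends Monday, 5 days.
- Reviewed Thursday: ends Tuesday, 5 days.
- Reviewed Friday: ends Wednesday, 5 days.

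The High ceiling is therefore 3 to 5 calendar days. Taking a week as 7 days, it is 7 − 5 = 2 to 7 − 3 = 4 days shorter than Moderate. It is 3 − 0 = 3 to 5 − 0 = 5 days longer than Severe. Public holidays would lengthen it.

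**3. The two readings of the action list**

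The article does not say whether the actions must be taken in the order listed.

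- *Not sequential.* Advice to the patient can go out at once while the GP notice is still within its limit. A patient who acts on it can arrive before the notice and the team's reading.
- *Sequential.* GP notice precedes patient advice in the High row, so the patient cannot arrive ahead of it. But the advice then sits behind a step that may take 3 working days.

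The limit is too loose for the label under either reading.

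**4. Who the change could still reach**

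The Results section gives the first enrolment in May 2021 and 112 of 200 enrolled as of December 2021. That leaves 200 − 112 = 88 to enrol. From 1 May to 31 December is at most 8 months, so nobody could have completed 12 months.

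**The case against.** The strongest reply has four parts.

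- **The listed order.** High puts GP notice before patient advice, and Severe puts the emergency department advice first. This may be deliberate, and if so it removes the early-arrival scenario. That stands, but it moves the delay to the patient instead of removing it.
- **Adjudication.** The High row has an adjudication step that the Severe row lacks, and its example is only a suspected finding. That is a plausible reason for a longer limit. It justifies time to confirm, but a notice marked as pending meets that need without holding back the first alert.
- **Mitigations.** An early-arriving patient carries the trace, the GP knows of the enrolment, and the article offers help from cardiologists. These stand and keep the point small. They are partial: the sentence on cardiologist help is framed around new AF, and a GP who has not been notified may not know to ask. The symptom advice does not cover a silent finding.
- **The Moderate row.** It pairs the same prompt-visit advice with a longer limit and is left alone here. That is true, but it is not labelled urgent.

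Some stronger readings are tempting and not supported. A reader might infer that the GP would have no tracing at all; the phone trace answers that. A reader might infer that Table 1 contradicts itself; the tiers are in order. A reader might cite the Background's remark on automated results exceeding people's competence; it concerns patients, not GPs, and lends no support here.

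**Conclusion.** The point holds as a minor one about participant safety. For findings the article itself calls urgent, and for which it names only the GP, the permitted time to GP notice is 3 to 5 calendar days under the Monday-to-Friday assumption. This is a maximum, not an expected delay: the team may act sooner, and the article does not say how often the High row would apply.

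A reader might infer that patients will be told late, or conversely that the limit can never delay them. Neither follows, because the article does not say whether the actions are sequential.

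**What to change.** In the High row, keep the instruction to notify and send the ECG to the GP, and replace the 3-working-day limit with: *on the same day, and no later than the patient is advised, marked as pending cardiologist confirmation or adjudication if not yet available*.

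The same-day clock is already used in the Severe row alongside a cardiologist consultation. The link to the patient's advice closes the gap whether or not the actions are sequential, and the pending mark means that neither message has to wait for confirmation. High and Severe still differ in where the patient is sent.

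The cost is a one-phrase table amendment, a notice to monitoring staff and possibly an ethics notification. No collected data change. As of the article's status date, it could still reach the 88 yet to enrol and everyone remaining in the program. The downside is faster turnaround for these tracings, and some GPs will be notified of a finding that is later not confirmed.

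### Table 1's Severe row advises immediate emergency attendance, but no step it lists promptly checks that the advice was followed (low-severity patient-safety improvement)

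*Protocol article*

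**What the plan says.** In the protocol article, under ECG Central Monitoring System, Table 1 sorts ECG findings by seriousness. Its third column is headed "The study team will take the following actions". The Severe row covers potentially life-threatening arrhythmias, with third-degree heart block as the example. It lists four actions:

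1. consult the team's cardiologists to confirm the diagnosis;
2. "Advise patients to present to their local emergency department immediately";
3. "Notify and send ECG to GP on the same day";
4. "Contact patient to confirm review with their GP in the subsequent week".

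The fourth line appears word for word in the Moderate and High rows as well. In those two rows the advice to the patient is "Advise patients to see their GP as soon as possible".

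Other parts of the article bear on what happens after an abnormal trace. Study personnel "will remotely review all ECGs and compare their diagnosis with" the device's own algorithm. In the section on the intervention group, "The research team will contact participants if they have not recorded any ECGs for 3 consecutive days". The same section gives standing advice: "Before commencing the study, participants will be advised that in the event of experiencing symptoms" that are severe or worrying, they should go to a local doctor or hospital. Data Collection places the further adverse-event enquiry at the end of the program, and the Appendix lists data collection at baseline, 6 months and 12 months.

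**The concern.** In the Moderate and High rows the follow-up contact closes the loop: the patient is told to see the GP, and the team then asks whether that happened. In the Severe row the advice changes to immediate emergency care but the follow-up does not. It asks about GP review, a different event. As listed, the table checks that advice was followed for the less serious classes and leaves this unchecked for the most serious one.

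What is at stake is participant safety. The Introduction itself recognizes that some participants may not follow up with a clinician after being notified of a significant abnormality, or may lack access to one. Participants are aged 75 or older, some are frail, they are recruited across wide areas of Australia, and all study procedures are remote. No member of the team sees the patient, so a call is the natural way to learn whether emergency advice was heeded.

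**Working it through.** No formula applies and there is no stated figure to reproduce. The check sets the rows of Table 1 side by side and then looks for any other step that would serve.

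**Step 1: advice against follow-up, by row**

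| Row | Advice to patient | GP notified | Patient follow-up listed | Does follow-up check the advice? |
|---|---|---|---|---|
| Moderate | See GP | Within a week | Confirm GP review | Yes |
| High | See GP | Within 3 working days | Confirm GP review | Yes |
| Severe | Attend emergency department now | Same day | Confirm GP review | No |

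The follow-up line is identical in 3 of 3 rows and matches the advice in 2 of 3.

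**Step 2: the Severe actions one by one**

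- Cardiologist consultation confirms the diagnosis, not attendance.
- The emergency advice is the instruction itself.
- Same-day GP notice informs the GP and assigns nobody to check attendance.
- The later contact confirms GP review.

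Actions that confirm emergency attendance: 0 of 4.

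**Step 3: timing of the one follow-up**

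The phrase about the subsequent week may date the contact or the GP review. On neither reading does the row set a same-day or next-day check of emergency attendance.

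**Step 4: other safeguards in the article**

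- *Same-day GP notice.* Helpful, but not a team check (see step 2).
- *Review of all ECGs.* A repeat abnormal trace would be seen, but only if the patient records again, and recording is scheduled for weekdays.
- *Contact after 3 consecutive days without ECGs.* It is triggered by silence. A patient who stays at home and keeps recording never triggers it, and one who stops recording is reached only after 3 days.
- *Symptom advice before the study.* It depends on the participant having severe or worrying symptoms and acting on them.

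Study-team checks of emergency attendance among these four: 0.

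Two further contacts do not help either. The GP contact about treatment follows the sentences on confirmed AF, has no timing and does not mention emergency care. The scheduled data collection and the end-of-program adverse-event enquiry come too late to be a prompt check.

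**Step 5: number affected**

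The article gives no rate of Severe findings and no rate of unheeded advice. No number can be derived, and none is assumed.

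**The case against.** The strongest reply is that nothing in the row is wrong. Confirming GP review is a reasonable continuity step, and it contradicts nothing. What remains is a missing call, and a journal article commonly leaves call-back timing and escalation to an operating procedure. The column header says that the team will take the listed actions; it does not say that it will take only those. Severe is also the most protective row, with cardiologist confirmation, direct emergency advice and the fastest GP notice, sent to a GP who has been told that the patient is enrolled. The later contact may well bring out what happened at the emergency department.

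Much of this stands. The GP-review line is not an error, the row is not careless, and a call-back may exist in a document not shown. This is why the point is rated low. The reply does not dispose of it entirely, because the article is not silent on follow-up after a Severe finding. It specifies one, and the event that it checks differs from the one advised. Incidental discovery during a GP-review contact is not the same as asking promptly.

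A reader might infer something stronger: that participants with life-threatening findings go unchecked in practice, or that the team plans to leave them for a week. The documents support neither. Table 1 shows what is listed, not everything that is done.

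**Conclusion.** The point holds as a cheap patient-safety improvement of low severity. Among the actions listed for Severe findings, none promptly checks that the emergency advice was followed, and the only patient follow-up concerns GP review. The sample size, outcomes, analysis and interpretation are unaffected.

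The conclusion rests on reading Table 1 as the stated action list and on finding no attendance check elsewhere in the article. It would fall away if the full protocol or an operating procedure already requires a prompt call-back; in that case Table 1 only needs to say so. The number of participants concerned is unknown and probably small. The case for acting rests on the seriousness of a single missed case and the low cost of the remedy, not on an estimated frequency.

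**What to change.** Add one line to the Severe row of Table 1: on the same day or the next day, study staff call the patient to confirm emergency department attendance, and log the answer. Keep the GP-review contact as the continuity step. If an operating procedure already contains such a call, cite it in the table instead.

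The cost is one extra phone call per Severe notification, made by existing staff. The change can be applied prospectively: the Results section reports 112 participants enrolled by December 2021 against a target of 200, so 200 − 112 = 88 had yet to join at that date.
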